**Results:**

Data on the primary variable (depressive symptoms) and secondary variables (treatment-related distress, anxiety, fear of hypoglycemia, quality of life, treatment adherence, coping strategies and glycemic control) will be collected from the TG at the beginning/baseline, at the end of treatment and at 3, 6 and 12 months after treatment. The CG will be assessed at the beginning and at the end of the TG intervention. On completion of the program by the TG, the treatment will then be carried out in the CG.

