Other authors have assessed the effectiveness of Web-based CBT treatment programs for the general population in individuals with diabetes. Robins et al. [35] designed a study in which they compared a 6-session Web-based treatment for the general population with a control group treated with usual treatment, obtaining positive results in mood and diabetes-specific distress, among others, but not in glycemic control. These results were maintained after 3 months of follow-up [36]. Clarke et al. [37] designed a study to evaluate the effect of a general population CBT program (myCompass) on the well-being of young people with type 1 diabetes. The results of this study have not yet been published. Nevertheless, they analyzed the results of this 7-session program in a pre-post study without a control group in a population with type 1 and type 2 diabetes and found significant improvement in depressive symptoms and specific distress, among other variables, although data on glycemic control were not collected [38] Thus, these treatment programs could also be offered as a possible avenue of intervention in people with diabetes.

According to previous studies, 21.7% of people with type 1 diabetes in our population have depressive symptoms [39]. There is a clear need to provide professionals with adequate tools to help people with this problem.

Based on the results obtained in previous studies, we have developed an Internet-based program for the treatment of mild-moderate depressive symptomatology for individuals with type 1 diabetes (WEB_TDDI1 study). In this study, we have created a specific program for people with type 1 diabetes including specific modules aimed at improving depressive symptomatology in this population and, indirectly, other variables related to depression in diabetes such as coping, anxiety, distress, and fear of hypoglycemia, which affect glycemic control, adherence to diabetic treatment and quality of life. This program has been designed specifically for individuals with type 1 diabetes because there are differential characteristics between type 1 and type 2 diabetes that should be considered separately [40] There are also important differences in their association with depression, suggesting that the associations are mediated by different underlying mechanisms [41] This article presents the design of this program and the methodology for its development and assessment.

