### Statistical analysis

First, a descriptive analysis will be conducted of the variables studied. For quantitative variables, measures of centralization and dispersion will be collected. For qualitative variables, a frequency analysis will be carried out.

To analyze cross-sectional and longitudinal differences, hypotheses will be contrasted at a 95% confidence level. To contrast differences between both groups (TG and CG) at baseline and post-treatment at a given time, Student’s *t*-test will be used (for strong violations of the normality assumption, the Mann-Whitney U-test) or analysis of variance (ANOVA). The effect size will be calculated using Cohen’s d.

To test whether the treatment produces differences over time (baseline, post-treatment, 3 months, 6 months and 12 months in the TG and baseline and post-treatment in the CG) in each of the groups, the *t*-test for related samples will be used (Wilcoxon signed-rank test in the event of strong violations of the normality assumption) or with an ANOVA for repeated variables and multiple regression model to control possible confounding variables (such as: age, gender, HbA1c, time with diabetes, etc.). For qualitative variables, McNemar’s test will be used.

To study the relationships between the different variables, Pearson’s correlation coefficient and linear regression models will be used for interval variables. The relationship between qualitative variables will be evaluated with the χ2 test.

Possible risk factors will be studied through logistic regression analysis (analysis of adherence to the treatment program).

The analyses will be carried out considering the subjects who complete the program. Analyses will also be carried out according to the protocol.

Analysis of the results will begin when the TG subjects have completed all of the phases of the treatment program. An improvement in the different variables will be taken into account in the following cases: significant differences in p≤0.05 and in the case of the BDI-FS when there is a decrease in the level of depressive symptomatology (moderate-mild, mild-minimum).

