We start from a treatment that is recognized as effective in the population in which it is to be applied [29–34] in depressive symptoms or depression and distress related to diabetes. However, no significant results were found regarding glycemic control, understood as the glycosylated hemoglobin (HbA1c) value. A possible explanation could be that, despite working with aspects related to the impact on the patient’s mood, changes in the treatment regimens for diabetes care are not directly addressed. This would make sense, as it is not the aim of this type of intervention. The study of other outcome variables of the web treatment on glycemic control, such as number of self-tests, episodes of hypoglycemia and hyperglycemia, and treatment adherence could add information along these lines. Moreover, other outcome variables with implications for treatment adherence, such as specific diabetes-related distress or fear of hypoglycemia, may also indicate structural changes that could influence long-term glycemic control. In addition, the number of sessions involved in treatment in previous studies has varied between 6 [32–36], 7 [37, 38] and 8 [29–31] treatment sessions. Based on previous studies and the existing relationships between depression and other variables in people with type 1 diabetes, in this study we have created 9 sessions.

Although it is known that adherence to Internet-based CBT treatment is lower than adherence when delivering the same treatment face to face [59], in the population with diabetes, there appears to be no difference between the two types of delivery [28]. Determining the variables involved in adherence to treatment will be among the data to be obtained in the present study. Accordingly, a comprehensive analysis of the medical and psychological variables involved in depression in people with diabetes, together with the variables that may affect adherence to this type of treatment in our study population, may help to provide greater insight into the effects of this treatment and the characteristics of the population in which it would be most beneficial (adherence), which are the main strengths of this study.

However, this study is not without limitations. The sample sizes of the previous studies are larger than the figure we aim to achieve in this study. Nevertheless, taking into account the rigor of the exclusion criteria and the sample size calculations described previously will enable reliable and valid conclusions to be drawn.

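### The only covariate adjustment is attached to the within-arm change, where the named covariates do no work, and the randomised comparison is given none

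*Protocol article*

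**What the plan says.** All references are to the Protocol article.

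- **Between arms.** Statistical analysis introduces this comparison with "To contrast differences between both groups (TG and CG) at baseline and post-treatment at a given time" and gives it a t-test, a Mann-Whitney test or an ANOVA, with Cohen's d as effect size. It names no covariate and no baseline score.
- **Within arms.** The next paragraph tests change over time, ending with "baseline and post-treatment in the CG) in each of the groups". The tools are a paired t-test or Wilcoxon test or, as an alternative, an "ANOVA for repeated variables and multiple regression model to control possible confounding variables (such as: age, gender, HbA1c, time with diabetes, etc". Control of confounders is mentioned nowhere else.
- **HbA1c as an outcome.** The abstract lists the secondary variables, ending with "quality of life, treatment adherence, coping strategies and glycemic control". The Discussion speaks of "glycemic control, understood as the glycosylated hemoglobin (HbA1c) value". Table 2 schedules clinical data and glycemic control at baseline, post-treatment and 3, 6 and 12 months.
- **HbA1c as downstream.** The Introduction names coping, anxiety, distress and "fear of hypoglycemia, which affect glycemic control, adherence to diabetic treatment and quality of life". Glycemic control is thus placed after the program's indirect targets.

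The article does not say whether the HbA1c covariate is the baseline or a time-updated value.

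**The concern.** Adjustment is useful where people who differ are compared. In a within-arm change each person is his or her own control. Gender does not vary within a person, and age and diabetes duration advance by the same amount for everyone. These variables may predict who changes more, but they cannot confound the mean change. A result labelled as controlled for confounders would look more secure than the plain pre-post difference while being the same number. The real threats to an uncontrolled change, such as natural recovery or regression to the mean, would be untouched.

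HbA1c differs from the other named covariates because it can respond to treatment. Conditioning on a post-baseline value of a trial outcome can remove part of the change being estimated.

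The comparison that randomisation supports, TG against CG after treatment, is left without covariates. With 28 per arm, precision is scarce and chance imbalance is plausible. Baseline covariates can help there, and they are already being collected.

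**Working it through.** The plan gives no figure for the effect of adjustment, so there is none to reproduce. From the document come 28 per arm, 56 in total, alpha 0.05 and effect size 0.50. All SDs, slopes, correlations and HbA1c shifts below are assumptions.

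**1. Fixed covariates in a within-arm model.** Regress each person's change on an intercept and covariates centred at the arm mean. Least squares gives

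intercept = mean change − Σ (slope × mean of centred covariate) = mean change − 0.

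This is an identity, whatever the data. It was checked in 4,000 simulated arms of 28 (assumed change −2, SD 2):

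| Model | Mean estimated change |
|---|---|
| Unadjusted | −2.006 |
| Age, gender, duration (centred) | −2.006 |
| The same plus baseline HbA1c (centred) | −2.006 |

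The largest difference from the unadjusted value in any run was 3 × 10⁻¹⁵, which is rounding error.

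**2. Time-updated HbA1c in a within-arm model.** If the change in HbA1c enters as a covariate,

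adjusted change = raw change − slope × mean HbA1c change.

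In the same simulation, with an assumed mean HbA1c change of −0.3, the estimate moved from −2.006 to −1.60, a shift of 0.41. Over a range, in BDI-FS points:

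- HbA1c change 0: shift 0 for any slope.
- Slope 0.5, change −0.1: shift 0.5 × 0.1 = 0.05.
- Slope 1.0, change −0.3: shift 1.0 × 0.3 = 0.30.
- Slope 1.5, change −0.5: shift 1.5 × 0.5 = 0.75.

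**3. What a good covariate buys in the randomised comparison.** With 28 per arm, d = 0.50, two-sided 0.05 and a normal approximation, unadjusted power is Φ(0.50 × √(28/2) − 1.96) = Φ(−0.09) = 46%. (That this is not 80% is a separate matter.) A baseline covariate correlated r with the outcome multiplies the residual SD by √(1 − r²):

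| r (assumed) | Variance factor 1 − r² | Power |
|---|---|---|
| 0.3 | 0.91 | 50% |
| 0.5 | 0.75 | 58% |
| 0.7 | 0.51 | 75% |

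The outcome's own baseline score is the natural first candidate.

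**4. What extra covariates cost.** With k covariates in N = 56 and two arms, the expected variance of the adjusted difference is multiplied by about (1 − R²) × (N − 3)/(N − 3 − k). For k = 4 the penalty is 53/49 = 1.082, so break-even is R² = 4/53 = 7.5%. If the baseline score is already in the model, the penalty is 52/48 = 1.083 and break-even is 4/52 = 7.7% of the remaining variance. Taking the four-covariate penalty of 1.082:

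- R² = 5%: (1/0.95)/1.082 = 0.97, a net loss of about 3%.
- R² = 10%: (1/0.90)/1.082 = 1.03, a net gain of about 3%.
- R² = 15%: (1/0.85)/1.082 = 1.09, a net gain of about 9%.

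**The case against.** The strongest reply is that a journal article need not state covariate timing or coding, and that on an ordinary reading (baseline HbA1c, sensibly coded) the adjusted within-arm estimate is simply the unadjusted one. The model is also only an option after a paired test. This stands as far as it goes, and the silence on timing alone would not be a finding. What the article does state is where the adjustment goes, and that is the wrong contrast.

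Four stronger readings are tempting, and the documents do not support them.

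- **That the planned adjustment will distort the result.** This needs a post-baseline HbA1c in the model and an HbA1c that moves. The Introduction and Discussion report that earlier web programs with glycemic data did not change glycemic control. The Discussion adds that this is not the aim of such interventions, and the Conclusions leave it out of the expected improvements. Zero loss is the case the article itself best supports.
- **That the adjustment can never remove bias.** This is shown only for the named fixed covariates and baseline HbA1c. The list is open-ended, and medication and habits, recorded at each assessment, vary over time and could confound a pre-post change.
- **That the unadjusted TG versus CG comparison is confounded.** Allocation is randomised. Omitting covariates costs precision and leaves chance imbalance, no more.
- **That raw, uncentred covariates would ruin the within-arm test.** The intercept would then stop being the mean change, but nothing in the article proposes testing it.

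It might also be argued that covariates could correct the completers-only analysis for selective dropout. In a check with age-related dropout (true change about −2.00, completers −2.26), adjustment centred on completers stayed at −2.26. Only standardising to everyone randomised recovered −2.00, and the article describes no such step.

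**Conclusion.** The point holds as one of misplaced adjustment. On the within-arm change, age, gender, diabetes duration and baseline HbA1c alter the estimated mean change by exactly zero when centred, so naming them as confounder control adds nothing. A time-updated HbA1c could remove 0.05 to 0.75 BDI-FS points if the slope is 0.5 to 1.5 and HbA1c falls by 0.1 to 0.5, and removes nothing if HbA1c is stable. In the randomised comparison, one baseline covariate with correlation 0.3 to 0.7 would raise power from 46% to between 50% and 75% at the planned effect. Four further covariates must explain roughly 7 to 8% of the variance before they help at all. The correlations, slopes and shifts are assumptions, since the article gives none. This is a better method available at almost no cost, not a flaw that invalidates the trial.

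**What to change.** In Statistical analysis:

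1. Move the adjustment to the post-treatment TG versus CG comparison as an ANCOVA. Enter the baseline score of the outcome first, then a short closed list of baseline covariates (for example age, gender, diabetes duration and baseline HbA1c). Delete the open-ended etc.
2. State that HbA1c is used as a covariate only at its baseline value and otherwise only as an outcome.
3. Report within-arm changes unadjusted, as description.

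This takes a few sentences and no new data. The cost is a few degrees of freedom in a 56-person model, with little or no net gain if the covariates beyond the baseline score are weakly prognostic. That is a reason to keep the list short.

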## Material and methods

### Study design and participants

This study is a longitudinal randomized control-group pretest-posttest clinical trial (S1 Table). Patients with type 1 diabetes who present depression (mild to moderate) and meet the inclusion criteria will be randomized through a computer program to 2 groups. The treatment group (TG) will receive the 9-week Web-based treatment, while the control group (CG) will comprise patients on the waiting list. Evaluations in the TG will be conducted at the beginning of the program (baseline), at completion and during follow-up (3, 6, and 12 months) after treatment. For ethical reasons, the CG will receive the Web-based treatment once the TG intervention has been completed. The CG will thus be assessed at the beginning and at the end of the TG treatment. At this point, the CG will begin treatment, provided the participants still meet the eligibility criteria, and will have their corresponding evaluations. The assessments will be conducted in person.

The participants will be individuals with type 1 diabetes from the province of Malaga (Spain) who meet the following criteria:

○ Inclusion criteria: medical diagnosis of type 1 diabetes ≥ 1 year; over 18 years of age; psychological diagnosis of mild/moderate major depressive disorder, dysthymia or depressive symptomatology; no concomitant pharmacological treatment that could modify blood glucose values or depressive symptomatology; no psychological treatment at the present time; absence of the following: chronic renal failure, impaired liver function tests, active thyroid disease (except correctly substituted hypothyroidism), current pregnancy or acute ketosis decompensation at the beginning of the study; Internet access.○ Exclusion criteria: type 2 diabetes; women who are pregnant or planning to become pregnant; severe macrovascular or microvascular complications; diagnosis of major depressive disorder with risk of suicide; non-collaboration (no signed informed consent); presenting a disabling psychiatric disorder; psychosis; no Internet access.

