### Sample size calculation

We calculated the effect size using Cohen’s [56] estimates for the calculation of sample size a priori. For this, the significance level was considered to be 0.05 and the power 0.80. Concerning the effect size, according to a recent review by Uchendu and Blake [14] on CBT in adults with diabetes, there is a moderate effect size (-0.43) in depression. Therefore, in our study, a moderate effect size (0.50) will be used. With these data, a sample size of 28 participants is needed. Since the study has 2 groups, 28 participants will be included in each of the groups (56 participants in total).

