## Conclusions

In this article, we present the design and methodology of the WEB_TDDI1 study, which includes a specific proposal for the treatment of mild-moderate depressive symptoms in adults with type 1 diabetes delivered through a Web-based CBT program. Based on previous studies, we anticipate an improvement in depressive symptomatology with respect to the control group and to baseline status, as well as an improvement in the secondary variables studied related to depression (anxiety, diabetes-related distress, fear of hypoglycemia, coping strategies, quality of life and adherence to diabetes treatment). Thus, this program is expected to provide professionals with a tool to treat mild to moderate depressive symptomatology in people with type 1 diabetes. Additionally, an analysis of the characteristics related to adherence to this program will be carried out to help establish profiles of people who will benefit from this type of treatment.

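### The article presents predictors of adherence to the web program as profiles of who will benefit, which a model fitted only in treated participants cannot show

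*Protocol article*

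**What the plan says.** Three places in the protocol article belong together.

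- Statistical analysis: "Possible risk factors will be studied through logistic regression analysis (analysis of adherence to the treatment program"). The predictors and their number are not listed.
- Discussion: the study of variables affecting adherence, together with the medical and psychological analysis, may give insight into "the characteristics of the population in which it would be most beneficial (adherence), which are the main strengths of this study". The word in brackets is the article's own gloss.
- Conclusions: an analysis of characteristics related to adherence to the program is added "to help establish profiles of people who will benefit from this type of treatment".

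Two further statements decide who could enter the model. The control group is treated later: "At this point, the CG will begin treatment, provided the participants still meet the eligibility criteria, and will have their corresponding evaluations". Yet "Analysis of the results will begin when the TG subjects have completed all of the phases of the treatment program". The article does not say whether controls treated later join the adherence analysis. Statistical analysis also says that the analyses consider participants who complete the program.

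**The concern.** Adherence and benefit are different quantities. A person may complete all nine sessions and improve no more than a similar person left on the waiting list. Another may stop early and still gain. A characteristic that predicts completion may therefore be unrelated to benefit, or even related to it in the opposite direction.

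The trial has a randomised control group, which is what a question about differential benefit needs, but the route proposed for that question does not use it. Followed as written, the plan could report a list of predictors of completion as guidance on whom to treat. With so few non-adherers, that list would also be unstable if more than one or two predictors were used.

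**Working it through.** **1. What each analysis estimates.** For a baseline characteristic x:

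- adherence model: P(adheres | given the program, x);
- benefit: mean outcome in the treatment group at x minus mean outcome in the control group at x;
- who benefits more: how that difference changes with x, that is, a treatment-by-x interaction on the depression outcome.

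During the randomised period the waiting list has no program to adhere to, so the first quantity contains no control information and cannot yield the second or third. Statistical analysis names no interaction or moderator analysis. (The treatment adherence scale under Results assessed measures diabetes self-care. It is a different construct from adherence to the web program.)

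**2. The plan's only sample-size figure.** Sample size calculation states "the significance level was considered to be 0.05 and the power 0.80", "Therefore, in our study, a moderate effect size (0.50) will be used" and "Since the study has 2 groups, 28 participants will be included in each of the groups (56 participants in total"). No size is given for the adherence model. Two groups at d = 0.50 need n = 2(1.96 + 0.84)²/0.50² = 63 per group two-sided (64 by the t-test), or 2(1.645 + 0.84)²/0.50² = 50 one-sided (51 by t). So 28 is not reproduced, and power with 28 per group is 0.45 two-sided by t. That is a separate point. Here it shows only that there is no spare capacity for secondary modelling.

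**3. How many predictors the data can carry.** Treated participants number 28 (treatment group only) to 56 (every control stays eligible and starts). The non-adherence rate is an assumption, taken from 10% to 50%. Non-adherers = N × rate. The number of predictors is that count divided by 10, a conventional rule of thumb, or by 5, a lenient one, rounded down.

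| Treated | Assumed rate | Non-adherers | Predictors at 10 each | Predictors at 5 each |
|---|---|---|---|---|
| 28 | 10% | 2.8 | 0 | 0 |
| 28 | 30% | 8.4 | 0 | 1 |
| 28 | 50% | 14.0 | 1 | 2 |
| 56 | 10% | 5.6 | 0 | 1 |
| 56 | 30% | 16.8 | 1 | 3 |
| 56 | 50% | 28.0 | 2 | 5 |

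**4. What happens beyond that.** Simulated predictors unrelated to adherence (400 data sets per setting, independent normal predictors, 30% non-adherence) gave these mean apparent AUCs, where 0.50 is the truth:

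- 28 treated: 0.59 with 1 predictor, 0.73 with 4, and 0.89 with 10 (24% of the ten-predictor fits were separated, and these were counted as AUC 1);
- 56 treated: 0.57, 0.65 and 0.76.

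**5. What one predictor can show.** The odds ratio per SD detectable with 80% power is exp[(1.96 + 0.84)/√(N·p(1 − p))], where p is the non-adherence rate. For p from 20% to 50%, this is 3.76 down to 2.88 with 28 treated, and 2.55 down to 2.11 with 56.

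**6. What an interaction could show.** With 28 per group and no missing data, the standard error of the main effect is √(2/28) = 0.267 SD. Ignoring any gain from baseline adjustment:

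- continuous moderator: the interaction per SD of moderator has the same standard error, 0.267, so the detectable value is 2.80 × 0.267 = 0.75 SD;
- moderator split in half (14 per cell): the standard error is √(4/14) = 0.535, so the detectable value is 2.80 × 0.535 = 1.50 SD.

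The plan assumes 0.50 SD for the whole treatment effect. The interaction would have to be 1.5 to 3 times as large to be found reliably.

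**7. Analysis set.** If the completer set applied to the adherence model as well, there would be little or no non-adherence left to model.

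**The case against.** The analysis is ancillary and its wording is hedged. It concerns possible risk factors, the Discussion says only that it may help give insight, and the strengths named there are plural and include the medical and psychological analysis. It is not the main objective. All of this stands, and it limits the severity. It does not rescue the link itself, because the Conclusions tie the adherence analysis directly to profiles of benefit and no choice of predictors could make that link valid.

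A reader might go further and infer that the planned model is heavily overfitted in about 28 people, or that screening the 24 personality scales (11 + 3 + 7 + 3) will produce false predictors. The document does not support this. It fixes no predictor list, number of predictors or screening rule. The scales under Results assessed are variables collected, not terms assigned to this model, and the p ≤ 0.05 rule defines improvement, not predictor entry. A list may sit in a fuller plan that is not shown, so its absence is no finding. Nor is 28 necessarily the number treated, since controls who remain eligible also receive the program. A model with one or two predictors would not be heavily overfitted.

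It is also fair to say that the alternative proposed here is weak. An interaction with 28 per group has little power.

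**Conclusion.** The point holds in this form: the Discussion and Conclusions read predictors of program adherence as profiles of benefit, and a model in treated participants only cannot support that reading. This part needs no assumption about rates or sample size.

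The overfitting part is conditional. Across an assumed 10% to 50% non-adherence and 28 to 56 treated (about 3 to 28 non-adherers), ten non-adherers per predictor allows at most one predictor with 28 treated and two with 56; at the lower rates it allows none. A larger model would be overfitted, but the article does not say that one will be fitted.

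Severity is low. The comparison of depression between the treatment and control groups does not depend on this analysis.

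**What to change.** - In Statistical analysis, Discussion and Conclusions, describe the logistic regression as an exploratory analysis of predictors of program completion, and remove profiles of people who will benefit as its product.
- Limit the model to one or two prespecified baseline predictors, with penalised (for example Firth) estimation and confidence intervals. With 28 treated, even one predictor falls below ten non-adherers unless non-adherence reaches 10/28 = 36%, which is why penalisation is advised.
- Fit it in everyone who starts the program, not in completers only, and state whether controls treated later are included.
- If who benefits is to be addressed, add one prespecified treatment-by-baseline interaction, for example with baseline BDI-FS, to the post-treatment comparison of the two groups. Label it exploratory and low-powered, and report the estimate with its confidence interval. Eligibility restricts BDI-FS to scores from 4 to below 13, which narrows the range over which such a moderator could act.

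The cost is rewording and a smaller model, with no new data. The downside is a less ambitious claim about patient selection and an interaction test that is unlikely to be conclusive.
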